## Abstract

**Introduction:**

Cervical cancer treatment can have life changing sequelae and be associated with poor short-term and long-term quality of life. Physical activity (PA; that is, bodily movement) is known to improve health outcomes and quality of life for cancer survivors, both physically and psychologically. To date, no interventions to increase PA following cervical cancer have been evaluated. This study aims to (1) determine the feasibility of conducting a PA intervention after cervical cancer and (2) to explore the acceptability of the programme and evaluation measures.

**Methods and analysis:**

The design is a pre study and post study design. Thirty participants aged between 18 and 60 years from the Midlands region, UK, who have completed primary treatment for cervical cancer at least 6 months previously and do not meet the national PA guidelines will be recruited. Identification of potential participants will take place through the University Hospitals of Leicester National Health Service (NHS) Trust. Participants will receive an intervention focused on increasing PA through the provision of education, action planning, goal setting, problem solving and self-monitoring of PA behaviour, particularly steps per day. Device assessed PA and questionnaires will be completed at baseline, week 6, week 12 and week 24. Feasibility will be assessed in terms of recruitment, retention, attrition, completion of measures and intervention compliance, for which specific feasibility criteria have been established. The process evaluation will explore the experiences and acceptability of the intervention components and evaluation measures.

**Ethics and dissemination:**

Ethical approval has been granted by the West of Scotland Research Ethics Committee 1 for this study. Results will inform intervention refinement for the design of a definitive pilot trial. These results will be disseminated via peer-reviewed publications and international conferences while input from a patient and public involvement (PPI) group will inform effective ways to circulate results among the wider community.

**Trial registration number:**

ISRCTN16349793, Registered 30 September 2020.

Strengths and limitations of this studyThe integration of behaviour change theory and insight from the target population to inform the development of practical strategies ensures an appropriate and user-friendly intervention.A mixed methods process evaluation will provide a great depth of understanding relating to the experiences and acceptability of the intervention and will enhance subsequent refinement where necessary.As this is a feasibility study, the analysis will not report statistically powered differences in outcomes (e.g., device-assessed PA).

## Introduction

Advancements in the clinical management of cervical cancer have resulted in improved survival,^1 2^ leading to a change in focus to treatment-related sequelae and survivorship issues, to reduce iatrogenic morbidity and to improve patients' long-term health.^3^ Although many patients diagnosed with a cervical cancer have early stage disease (stage IA), which can be successfully treated with local excision, 64% of women have at least stage IB disease at diagnosis.^4^ As a result, many patients will need to undergo radical surgery and/or chemoradiotherapy, that consequentially leads to the loss of fertility and an early menopause.^3^

The long-term effects of radiotherapy on the vagina,^5^ bladder^6^ and bowel can occur in between 30% and 40% of patients and can result in distressing symptoms, urinary/faecal such as incontinence^7^ and tenesmus.^8^ It can also lead to permanent physical changes, vaginal shortening/stenosis and reduced clitoral sensitivity, thereby physically limiting the ability to have and enjoy intercourse.^9^ Chronic fatigue and pelvic insufficiency fractures are also frequently reported following radiotherapy treatment for cervical cancer, the symptoms of which may not diminish with time,^10^ and can have a negative impact on daily functions and social quality of life.^11^

There is also substantial evidence of the devastating psychological consequences of a cervical cancer diagnosis. A high proportion of patients experience long-term psychological distress following their diagnosis,^12^ which can impact on their social, work and functional well-being. The psychological impact is more pronounced in younger patients and those who receive chemoradiotherapy,^13^ with reported lower levels of self- confidence and a more negative body image compared with those who undergo surgery alone.^14^ Hence, a greater focus on cervical cancer survivorship is warranted to support patients who are living alongside the physical, psychological and social impacts of cervical cancer treatments.

Identifying and implementing ways to manage treatment side-effects can be challenging, given the individualistic and complex nature of the survivorship experience.^15^ Moreover, concerns have been raised regarding the knowledge provision of treatment-related morbidity and clinical support services.^16^ Physical activity (PA), defined as *‘*any bodily movement produced by skeletal muscles that results in energy expenditure’ (17 p126) has been shown to be a safe avenue to improve quality of life following cancer treatment,^18^ with qualitative data indicating that PA can specifically improve physical, psychological, social and spiritual domains.^19^ However, PA levels are reportedly low and remain low up to 3 years following treatment for a gynaecological malignancy.^20^ In particular, cervical cancer survivors meet recommended PA guidelines less frequently than patients following other cancer types.^21^ Exercise recommendation for cancer survivors have been suggested^22^; however, these do not target the specific PA barriers faced after cervical cancer, thus supporting the need for tailored PA promotion in this population.

To date, there has been little research focus on promoting PA among those treated for cervical cancer. This is highlighted by cervical cancer cases being underrepresented in meta-analysis studies of gynaecological cancer.^18^ Literature based in the broader context of gynaecological cancer and PA does provide some degree of insight regarding PA preferences and feasibility of different types of PA. Such studies suggest that PA which: incorporates home-based walking,^23–25^ and gym activities^25^; is graded and flexible^24^; is combined with a form of support or counselling^24^; includes social interaction with peers,^26^ tends to be favourable among survivors of gynaecological cancers. There is growing support for technology-based PA promotion among cancer survivors,^27^ which can place less burden on participants, and can be easily tailored to the individual. However, the PA barriers faced after cervical cancer may differ to other gynaecological cancers due to variations in patient characteristics (e.g., age) and treatment side effects. Therefore, it is important to consider the specific needs of cervical cancer survivors during intervention design and implementation.

To the best of our knowledge, an intervention which promotes PA participation following treatment for cervical cancer has not been evaluated. Therefore, we aim to test the feasibility and acceptability of conducting and evaluating a multicomponent intervention programme, informed by relevant theories of behaviour change, to increase PA levels following treatment for cervical cancer. This intervention has been named: Acceptability in Cervical Cancer of an Exercise-based Programme delivered Through An oNline Community Environment (ACCEPTANCE). This intervention was developed using the intervention mapping protocol.^28^

### Aim

The overall aim of this study is to assess the feasibility and acceptability of a PA intervention following treatment for cervical cancer.

#### Objectives

To determine participant recruitment, retention and attrition rates.To review descriptive data to determine the feasibility of the inclusion criteria.To determine compliance and completeness of evaluation measures at all time points.To report the feasibility of delivering the intervention and evaluation measures.To explore participant compliance with the intervention.To obtain views on the acceptability of the intervention and evaluation measures.To describe device-assessed PA levels and questionnaire data outcomes of interest.

## Methods and analysis

### Study design

This is a single-arm pre study and post study to assess the feasibility and acceptability of conducting and evaluating a PA intervention following treatment for cervical cancer. A process evaluation will also be conducted throughout the study.

### Study setting

This study will be conducted through the University Hospitals of Leicester (UHL) National Health Service Trust, in collaboration with Loughborough University and the University of Leicester.

### Patient and public involvement (PPI)

PPI consisted of two groups of women treated for cervical cancer within the previous 10 years. PPI input has informed the development of the study since its inception. Insights and feedback gathered from one to one and group discussions with PPI members enabled development of the research question, assessment of the potential burden on participants and informed the intervention content to ensure that intervention materials were user friendly (table 1).^29^ Continuation of PPI involvement will inform the intervention delivery and dissemination of results to the wider community as appropriate.

**Table 1 T1:** Patient and public involvement (PPI) involvement and engagement in research activities

Research stage	Involvement	Mode
Research conception and design	Establishment of unmet needs after cervical cancer	In person group discussion PPI+RT
	Sharing personal experience of recovery after cervical cancer	One to one conversation PPI+SC
Recruitment for feasibility trial	PPI members provide feedback on recruitment poster	Email correspondence PPI+SC
	PPI members share study details via word of mouth or poster on online survivorship group	Email correspondence PPI+SC
Intervention design	PPI group to provide feedback on the feasibility of the intervention timeline	Group discussion between PPI+SC; use of questionnaire to elicit feedback
	PPI members to complete evaluation questionnaire and provide feedback on length and language use	One to one in person conversation PPI+SC
	PPI group to evaluate intervention materials (diary, education and *fitbit* guide)	Email correspondence PPI+SC
	PPI group to complete intervention launch session and provide feedback	Virtual group discussion PPI+SC
Programme delivery	PPI group to feedback on progress of intervention at mid-intervention delivery	Virtual group discussion PPI+SC
Dissemination of results	PPI group to feedback on appropriate strategies to disseminate results to the wider public (including patients and survivors)	Virtual group discussion PPI+SC

RT, research team; SC, study coordinator.

### Participants and recruitment

Participants between the ages of 18 and 60 years who have undergone treatment for cervical cancer at least 6 months previously with curative intent (either surgery, chemoradiotherapy or both modalities), who do not meet the national PA guidelines (150-300 min of moderate to vigorous intensity PA per week),^30^ who can gain permission from their gynaecologist/oncologist to take part and are proficient in speaking English will be recruited. The age range of 18–60 years was chosen to reflect the Chief Medical Officer’s PA adult guidelines and to optimise engagement and adherence to a technology-based PA programme. Exclusion criteria are benign or premalignant (cervical interepithelial neoplasia) disease of the cervix; clinical/radiological evidence of disseminated malignancy; pregnancy or breast feeding; performance status ≥3; comorbidity that in the opinion of the patient’s supervising gynaecologist/oncologist would preclude the patient from meeting the study requirements.

Initial database screening will take place by the clinical gynaecological oncology team to identify candidates who are at an appropriate age and stage in their treatment journey. Potentially eligible participants will be approached through their clinical team; recruitment posters will be placed in the gynaecological and oncology outpatient departments at UHL; and study details (overview of research, inclusion criteria and relevant contact details) will be posted on social media platforms. Local cervical cancer support groups will also be contacted and given information on the study to raise awareness of the research. Screening will take place via a telephone call with a member of the research team. The Scottish Physical Activity Questionnaire^31^ will be used to determine PA levels. Participants will be asked how many minutes per week they spend being active at a moderate intensity in the context of the last 7 days. Consent procedures will take place either virtually via video/telephone call or in person at UHL.

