### Sample size

This study will aim to recruit approximately 30 participants. This sample size was chosen as it is a realistic target when considering cervical cancer incidence both in the UK and at UHL where recruitment will take place over the given time period. In line with recommendations from the National Institute for Health Research, a sample size of 30 is appropriate to answer the questions posed by a feasibility trial.^32^ The feasibility of lifestyle and PA interventions in endometrial and breast cancer survivors have successfully employed similar sample sizes.^27 33^

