#### PA and health measures

An accelerometer (GENEActiv, Activinsights) and sleep log will be administered at all evaluation time points to measure PA. Participants will be asked to wear the accelerometer on their non-dominant wrist 24/7 for 8 days at each time point. Valid data will be at least 3 days >16 hours of accelerometer data collected.^39^ Device-assessed PA will be the primary research outcome measure of interest in the subsequent pilot study and definitive main trial.

Participants’ belief in their ability to successfully complete incremental 5–50 min periods of walking at a moderate/brisk pace will be assessed via the self-efficacy for walking scale.^40^ Motivation for PA will be assessed using the Behavioural Regulation in Exercise Questionnaire.^41^ This is a 23-item scale which assesses motivation on a self-determination continuum. Enjoyment of PA will also be assessed via the original 18-item PACES scale.^42^

In relation to well-being, menopausal symptoms, such as hot flushes and sweating will be investigated using the Menopausal Rating Scale.^43^ Quality of life will be assessed using the EORTC QLQ-30, which is commonly used in gynaecological cancer populations and includes five functional scales, three symptom scales, a global health scale and a quality of life scale. The Hospital Anxiety and Depression scale (HADS),^44^ will be administered to measure symptoms of anxiety and depression. Fatigue will be assessed using the Multi-dimensional Fatigue Symptom Inventory (MFSI-SF),^45^ a measure which has been previously used to assess fatigue in a gynaecological cancer population.^23^

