### Statistical analysis

As this is a feasibility study, main analyses will use descriptive statistics. Data will be analysed using *IBM SPSS statistics V.25*.

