#### The feasibility of inclusion criteria

We have suggested that if an eligibility criterion accounts for 40% of ineligibility, it will be reported.

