#### The feasibility of study recruitment and retention

A priori, we have defined a recruitment success rate as recruitment of 30 participants in the first 3 months or that 75% of those identified as eligible are recruited, and a successful retention rate at week-24 as 70%.

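### Eligibility is defined on moderate-to-vigorous activity, but the screening question as described asks only for moderate minutes, so some women who already meet the guideline could be enrolled

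*Protocol article*

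**What the plan says.** Under Participants and recruitment, the protocol article limits entry to women "who do not meet the national PA guidelines (150-300 min of moderate to vigorous intensity PA per week". The same section says that the Scottish Physical Activity Questionnaire "will be used to determine PA levels" during a telephone screen, and that women will be asked "how many minutes per week they spend being active at a moderate intensity in the context of the last 7 days". It does not reproduce the questionnaire's items or scoring, and it does not say whether vigorous minutes are added to the answer.

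The planned size is stated under Sample size: "This study will aim to recruit approximately 30 participants". Two pre-set feasibility rules use the result of screening. For the inclusion criteria, "if an eligibility criterion accounts for 40% of ineligibility, it will be reported". For recruitment, success is 30 participants in the first 3 months, or that "75% of those identified as eligible are recruited". An accelerometer "will be administered at all evaluation time points to measure PA", baseline included, but it is not described as a check on eligibility.

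**The concern.** The criterion and the question that applies it refer to different quantities. The criterion is about moderate and vigorous minutes together; the question, as worded in the article, is about moderate minutes. A woman whose activity is largely vigorous can be above the guideline on the first and below it on the second.

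This is more than a detail left to a fuller document. The article itself gives the instrument, the recall period and the intensity, and that intensity differs from the one in the criterion in the same section.

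At stake are the outputs that depend on correct classification at screening. The study lists the feasibility of its inclusion criteria among its objectives, so an error in applying one of them bears on a stated aim. Device-assessed activity is also to be the primary outcome of the later trials, so its baseline mean and SD should describe women who meet the stated criterion.

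**Working it through.** The article gives no figure to reproduce here: the sample size of 30 is justified by feasibility and precedent, not by a calculation. The check compares two statements and then traces the consequences.

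**Inputs.** M = moderate minutes per week and V = vigorous minutes per week, both over the last 7 days. The cut-off is taken as 150, the lower bound of the article's range. The sample is 30.

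**Classification.**
- By the criterion, a woman is eligible if M + V < 150.
- By the question as described, she is eligible if M < 150.
- The two disagree when M < 150 and M + V ≥ 150.

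| M | V | M + V | By the criterion | By the question |
|---|---|---|---|---|
| 60 | 120 | 180 | not eligible | eligible |
| 100 | 60 | 160 | not eligible | eligible |
| 0 | 150 | 150 | not eligible | eligible |

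The error runs one way. Since V cannot be negative, the narrower question can wrongly admit a woman but cannot wrongly exclude one.

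**Size.** Each misclassified participant is 1/30 = 3.3% of the sample. The article gives no figure for how common such women are. Taking 0%, 5% and 10% of those enrolled, purely as assumptions, gives 0, 0.05 × 30 = 1.5 and 0.10 × 30 = 3 of 30.

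**Effect on the 40% rule.** Suppose A of I ineligible women are excluded on activity, with one reason counted per woman, and k more should have been. The reported share is A/I; the correct share is (A + k)/(I + k). The correct share is larger whenever A < I and k > 0, so the part played by the activity criterion is understated.

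**Effect on the 75% rule.** The threshold is met exactly by 30 recruited of 30/0.75 = 40 eligible. If one of those 40 was misclassified and enrolled, the correct figure is 29/39 = 74.4%. If she was misclassified and declined, it is 30/39 = 76.9%. The direction is therefore not fixed, and one woman moves the rate by less than 2 percentage points, which matters only close to the threshold.

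**Effect on baseline activity.** Women already at the guideline would be expected to raise the baseline mean. The article gives no mean or SD from which to calculate by how much.

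**Is there a later check?** The baseline accelerometer is the only candidate. The sections PA and health measures and PA data and questionnaire outcomes use it for description only, with no rule to confirm or revoke eligibility.

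**The case against.** The strongest reply is that the article names a whole questionnaire and then summarises it in one sentence. The moderate intensity in that sentence may be shorthand for at least moderate, respondents may include vigorous minutes in their answer, and the scoring may be set out in a full protocol that is not shown. This stands in part. It rules out saying that vigorous minutes are never counted, or that active women will be enrolled; the text supports only that they could be. It does not remove the mismatch, because the article's own description of the question is narrower than its criterion. Nor is it safe to rely on respondents to read the question broadly: what moderate activity feels like is taught at the intervention launch (Table 2), not at screening.

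A second reply is that few women will be affected. The Introduction reports low activity after gynaecological malignancy and says that cervical cancer survivors meet the guideline less often than patients with other cancers. This stands, and the number may be near zero.

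A third is that the study is small and single-arm, and that "As this is a feasibility study, main analyses will use descriptive statistics". No test result is biased, and the baseline accelerometer could show an already active subgroup before the next trial. This also stands, and it limits the harm. It would show the problem only after enrolment, however, and would not correct the screening counts.

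A reader might also infer that the range 150-300 leaves the cut-off open. That is weak: failing to meet such a guideline is naturally read as falling below 150.

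**Conclusion.** The point holds as an inconsistency within one section of the article. The criterion counts moderate and vigorous minutes, the screening question as described asks for moderate minutes, and no later step checks eligibility. Women who meet the guideline through vigorous activity could therefore be enrolled as insufficiently active.

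The likely effect is small: about 3.3% of the sample for each such woman, with an unknown number that may be zero. The distortion falls on the inclusion-criteria review, the recruitment rate among eligible women and the baseline activity description. The conclusion assumes that the question is put as the article words it and that 150 minutes is the cut-off.

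A reader might go further and infer that the study would describe the wrong population, or that already active women would comply more easily and so flatter compliance and retention. The documents do not support either. They give no prevalence of vigorous activity and no evidence linking prior activity to compliance. The intervention targets walking and steps, which can still rise in someone whose minutes come from vigorous activity.

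**What to change.** At the existing telephone screen, ask for both moderate and vigorous minutes in the last 7 days, add them, and apply the criterion to the total: eligible if below 150 minutes, the article's own lower bound. Record the total for every woman screened, so that the counts behind the 40% and 75% rules can be checked. If the questionnaire as used already adds vigorous minutes, a sentence saying so is enough.

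The cost is one extra question and one line of protocol text. The downside is possibly a few more screen-outs, all of them women whom the stated criterion already excludes.
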